### Data collection and data analysis

In this study two sources of electronic data are used. The DECU gives a detailed overview of the intervention and follow-up period and contains the data from the questionnaires, assessments and e-consultations. Additional patient data is extracted from the electronic patient file in the Wilhelmina Children’s Hospital. After data collection, all data will be combined into one SPSS (Statistical Product and Service Solutions) database.

Data will be analyzed on an intention to treat basis. To examine whether there is a significant difference on the primary outcomes between the intervention and control group, a mixed-effects regression model will be used. Fixed effects for time, intervention group and the time*group interaction will be included in the model in order to examine the differences between the groups over time. To adjust for possible curvilinearity a squared term for time will be included in the model. A random intercept and random slope per child will be included in order to account for repeated measures within children. Baseline values of the outcome variables are included as fixed covariates to examine their possible impact on the observed treatment effect.

Data relating to asthma outcomes will be analyzed separately for all children diagnosed with asthma. All analyses conform to a specified plan. There are no interim analyses or stopping rules.

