All children in both interventions are discussed in weekly videoconferencing sessions with both multidisciplinary teams. AD treatment in both interventions is supervised by a single dermatologist in the Netherlands to minimize differences. Corticosteroid use is reduced or increased according to similar stepwise plans in both treatment arms. The educational plan is co-developed by both centers and consists of similar elements in both treatment arms. It is administered by the nurse and there is frequent contact between the nurses of both treatment arms.

The pragmatic nature of our trial will not allow us to find out how or why the interventions work, or which elements of the interventions contribute most to the observed treatment effects. Therefore we will study effectiveness: the long-term benefit of either treatment in routine clinical practice [31].

This study has several strengths. Children that participate come from all over the Netherlands. They often have an extensive treatment history and still experience an impaired quality of life, despite treatment according to current guidelines. In this study, children receive multidisciplinary treatment with individualized treatment goals either in their own environment or in an alpine clinical environment. The results of this trial will show which would be the most appropriate approach to provide treatment that results in sufficient long-term disease control for children with difficult to treat AD. The findings of our trial will be directly applicable in practice in the Netherlands.

The study also has potential drawbacks. It is an intense period for the study participants in which they have to visit the Wilhelmina Children’s Hospital several times for the scheduled assessments. Each assessment means a missed day of work for the parents and a missed school day for the child. This may lead to a larger drop-out rate than anticipated and it may take a lot of effort to keep the study participants motivated for all assessments. In this study neither the study participants nor the healthcare professionals assessing outcomes were blinded to the received intervention. This may cause bias for the more subjective outcome measures, such as the SA-EASI.

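### The primary model allows the arms to differ only along a straight line in time, and leaves open which contrast is tested and whether T0 is a response

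*Protocol article*

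**What the plan says.** The section on data collection and data analysis in the protocol article gives one model for all primary outcomes:

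- Arm and time: "Fixed effects for time, intervention group and the time*group interaction will be included in the model", with the purpose "in order to examine the differences between the groups over time".
- Curvature: "To adjust for possible curvilinearity a squared term for time will be included in the model". No product of this term with group is mentioned.
- Within-child dependence: "A random intercept and random slope per child will be included".
- Baseline: "Baseline values of the outcome variables are included as fixed covariates". The text does not say whether the baseline visit is also an outcome row.

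The sections on design and follow-up give a six-week intervention with assessments directly after it (T1), six weeks after it (T2) and six months after it (T3). Table 2 adds T0 before the start. The Discussion describes the aim as "the long-term benefit of either treatment in routine clinical practice". No coefficient or visit is named as the primary contrast.

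**The concern.** The authors foresaw curvature but placed the term where it cannot affect the treatment comparison. A squared term shared by both arms cancels when one arm is subtracted from the other. What remains is the group coefficient plus the interaction coefficient multiplied by time, which is a straight line.

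The treatment stops at week 6 and follow-up runs to about week 32. A difference that is absent at T0, present at T1 and then sustained or declining is a plausible course, and it is not linear across these visits. The model could then report a difference before treatment that does not exist, understate the difference at the end of treatment, and spread a waning effect into a nearly flat line. This would affect coping, quality of life and disease activity alike.

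**Working it through.** **Inputs.** From the sample size section: difference 5, SD 7.6, 36 per arm. From the design section: weeks 0, 6, 12 and 32 (six months taken as 26 weeks). Assumed: two-sided 5% level, equal within-child correlation 0.6, complete data, time in weeks from T0, normal approximation.

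**The plan's own figure.** For two means, n = 2(1.96 + 0.84)² × SD²/difference².
- Coping, 5 points and SD 7.6: 36.3 per arm (power at 36 about 79.7%).
- Disease activity, 10 points and SD 15: 35.3, so 36.
- 36/0.9 = 40.

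The stated 36 and 40 are reproduced, as a comparison of two means.

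**How the difference is fitted.** With complete data and a random intercept and slope, the fitted difference is the ordinary least-squares line through the true differences, whatever the variance components. The same holds under equal correlation.

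**Reading A: T0 is also a response.** Mean week 12.5; deviations −12.5, −6.5, −0.5, 19.5; sum of squares 579.

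For 0/5/5/5:
- slope = 5(−6.5 − 0.5 + 19.5)/579 = 0.108 per week
- value at T0 = 3.75 − 0.108 × 12.5 = 2.40

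For 0/5/4/2.5:
- slope = (−32.5 − 2 + 48.75)/579 = 0.0246
- value at T0 = 2.875 − 0.0246 × 12.5 = 2.57

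Standard error of the slope = √[2 × 7.6² × 0.4/(36 × 579)] = 0.0471. The ratios are 2.29 and 0.52, giving interaction power of 63% and 8%.

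For the joint 2-df test, the variance of the mean difference is 2 × 7.6² × 0.7/36 = 2.246. The noncentrality for 0/5/4/2.5 is 2.875²/2.246 + 0.52² ≈ 3.95, giving 41% power. For 0/5/5/5 it is 3.75²/2.246 + 2.29² ≈ 11.5, giving 87%.

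| True T0/T1/T2/T3 | Fitted | Interaction power | Joint power |
|---|---|---|---|
| 0/5/5/5 | 2.40/3.05/3.70/5.85 | 63% | 87% |
| 0/5/4/2.5 | 2.57/2.72/2.86/3.35 | 8% | 41% |
| 0/5/2.5/0 | 2.60/2.25/1.90/0.74 | 24% (negative slope) | 33% |

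These powers ignore any gain in precision from the baseline covariate.

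**Reading B: only T1 to T3 are responses, baseline as covariate.** Mean week 16.67; sum of squares 370.7; slope standard error √[2 × 7.6² × 0.4/(36 × 370.7)] = 0.0588.

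| True T1/T2/T3 | Fitted | Interaction power | Joint power |
|---|---|---|---|
| 5/5/5 | 5/5/5 | 5% | 99% |
| 5/4/2.5 | 4.80/4.26/2.44 | 34% | 94% |
| 5/2.5/0 | 4.37/3.32/−0.19 | 85% | 93% |

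The largest error is 3.32 − 2.5 = 0.8 points, at T2. For 5/5/5 the group coefficient, with time counted from T0, has about 93% power. A baseline-adjusted contrast at one visit has standard error 7.6√[2(1 − 0.36)/36] = 1.43 and about 94% power for 5 points. An effect gone by T2 (5/0/0) would be distorted more, fitted as about 3.2/2.35/−0.55.

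**Sensitivity, reading A.**
- Autoregressive correlation 0.75: interaction power 34% for 0/5/5/5 and 5% for 0/5/4/2.5.
- The plan's random intercept and a modest random slope: 49% for a sustained effect (39% to 68% as the intercept share runs from 0.3 to 0.7).
- Time coded as visit number 0 to 3: 0/5/5/5 is fitted as 1.5/3/4.5/6, so the misfit changes but remains.

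**The case against.** The strongest reply is that the article never names the interaction as the test. Group is also in the model. Entering baseline as a covariate suggests that only the later visits are responses, and under that reading a sustained benefit is fitted exactly and the group or joint test detects it. The article also refers to a specified plan that is not shown and may name the contrast. This largely stands, and it rules out two stronger statements that a reader might infer:

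- **That the analysis would entirely miss a real benefit.** This is true only of the time*group term taken alone, and the text does not make that the sole test.
- **That the model gives no estimate at any visit.** It gives one at every visit; the estimate is simply bound to a line.

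It is also fair that the course of the effect is assumed. No passage predicts it, and a difference that built up steadily through follow-up would suit a linear contrast. The power figures depend on assumed correlations; the fitted profiles under the plan's own random effects do not.

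The reply does not remove the constraint. The model is written out term by term, curvature is named, and the term that would let curvature differ by arm is not among those listed. The wording on baseline does not exclude T0 as a response, where the misfit is large.

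**Conclusion.** The point holds as a weakness of the model as stated. The between-arm difference is forced to be linear over unequally spaced visits, and its cost depends on two things that the article leaves open.

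- With T0 as a response, a sustained 5-point effect acquires a false 2.4-point difference before treatment and loses about 2 points at T1. A partly waning effect leaves the interaction close to its 5% error rate, and even the joint test is well below 80%.
- With T1 to T3 only, the error is at most about 0.8 of 5 points for the sustained and steadily waning profiles. The remaining risk is that time*group alone is read as the test of a sustained benefit, for which it has no power beyond 5%.

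These sizes rest on 36 per arm, SD 7.6, correlation 0.6, a two-sided 5% level and the profiles shown.

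**What to change.** State that baseline is a covariate only and not an outcome row. Model the post-treatment visits T1, T2 and T3 as categories with group-by-visit terms. At the least, add time-squared*group; with three response visits this already leaves the three differences unconstrained. Name in advance the adjusted group contrast that is the primary test, in place of the linear interaction. The six-month visit would fit the stated long-term aim, but the choice is the sponsor's. The covariance structure, whether to keep the random slope, and which pre-treatment visit serves as baseline are separate choices that this point does not decide.

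The cost is a change of analysis wording and a few more parameters. No visit, measurement or sample size needs to change for it. A joint test over three visits gives up a little power where the linear form happens to fit: for 5/5/5 with T1 to T3 as responses it has 98%, against 99% for the linear joint test.

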## Discussion

The DAVOS trial is a pragmatic randomized controlled trial that investigates the effect of multidisciplinary treatment at high altitude compared to sea level on coping, quality of life and disease activity in children with moderate to severe AD within the atopic syndrome. It is designed as a pragmatic trial, which fits best with our objective to find a new intervention with optimal treatment results for children with difficult to treat AD [31]. In this study we compare inpatient treatment in a high altitude clinic in Switzerland with outpatient treatment in a national expert center in the Netherlands. We chose for outpatient treatment in the Wilhelmina Children’s Hospital, because it currently offers the most specialized and intensive treatment in the Netherlands for this group of patients. It is most efficient to organize the involved medical disciplines to see the patients consecutively in an outpatient setting. Furthermore, we want to evaluate the best treatment for children with difficult to treat AD that minimizes the burden but maximizes the result. This means that if it is possible to reach significant clinical improvement with an intense six week outpatient program in the Netherlands, this is the preferred choice compared to a six week inpatient treatment in the Netherlands. Also, it would not be possible to extrapolate results from inpatient treatment in an academic hospital compared to a peripheral hospital. We believe that in this trial design, we are comparing the best options for treatment that are also likely to be carried out in practice after the end of the trial.

There are several differences between the intervention and control conditions, such as the differences in setting: inpatient and outpatient, own environment and change to alpine environment. During the intervention in Davos, adherence to treatment is more likely to increase due to the clinical setting. Children are separated from their parents which can be perceived as an extra burden for the child. It may also be an advantage, especially when the coping strategy of the child is negatively influenced by the coping strategies of the family [32].

All children in both interventions are discussed in weekly videoconferencing sessions with both multidisciplinary teams. AD treatment in both interventions is supervised by a single dermatologist in the Netherlands to minimize differences. Corticosteroid use is reduced or increased according to similar stepwise plans in both treatment arms. The educational plan is co-developed by both centers and consists of similar elements in both treatment arms. It is administered by the nurse and there is frequent contact between the nurses of both treatment arms.

The pragmatic nature of our trial will not allow us to find out how or why the interventions work, or which elements of the interventions contribute most to the observed treatment effects. Therefore we will study effectiveness: the long-term benefit of either treatment in routine clinical practice [31].

This study has several strengths. Children that participate come from all over the Netherlands. They often have an extensive treatment history and still experience an impaired quality of life, despite treatment according to current guidelines. In this study, children receive multidisciplinary treatment with individualized treatment goals either in their own environment or in an alpine clinical environment. The results of this trial will show which would be the most appropriate approach to provide treatment that results in sufficient long-term disease control for children with difficult to treat AD. The findings of our trial will be directly applicable in practice in the Netherlands.

The study also has potential drawbacks. It is an intense period for the study participants in which they have to visit the Wilhelmina Children’s Hospital several times for the scheduled assessments. Each assessment means a missed day of work for the parents and a missed school day for the child. This may lead to a larger drop-out rate than anticipated and it may take a lot of effort to keep the study participants motivated for all assessments. In this study neither the study participants nor the healthcare professionals assessing outcomes were blinded to the received intervention. This may cause bias for the more subjective outcome measures, such as the SA-EASI.

To the best of our knowledge, this is the first randomized trial that compares high altitude treatment with treatment at sea level in children with difficult to treat AD. Our study provides new and detailed information on the characteristics of these children. We hope to provide evidence for an intervention that gives the best results in terms of coping, quality of life and disease activity for this group of children.

## Trial status

The first patient was included in the study in September 2010. At the moment patient recruitment and data collection is in progress. We expect to complete patient recruitment by May 2014.

## Abbreviations

AA: Allergic asthma; ACQ: Asthma control questionnaire; AD: Atopic dermatitis; BHR: Bronchial hyperresponsiveness; CDQLI: Children’s dermatology quality of life index; DECU: Digital Eczema Center Utrecht; FeNO: Fraction of exhaled nitric oxide; FEV1: Forced expiratory volume in one second; FVC: Forced vital capacity; JUCKKI/JUCKJU: Itching cognitions questionnaire; PAQLQ: Pediatric asthma quality of life questionnaire; (SA)-EASI: (Self-administered) Eczema area and severity index; SAS: Statistical analysis software; SCORAD: Scoring atopic dermatitis; SD: Standard deviation; TARC: Thymus and activation-regulated chemokine.
